## 2. OBJECTIVES

### Primary Objective:

- To determine the acute and chronic effects of pure epicatechin and quercetin-3-glucoside on vascular and endothelial function – as measured by Flow-Mediated Dilation.

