### 3. STUDY DESIGN

#### Part 1 (Supplement Study):

The study will be undertaken as a three-armed, placebo-controlled, double-blind, cross-over trial. At the start of the study, participants will be asked to follow a 1-week run-in period during which they will be given dietary advice to avoid the consumption of flavonoid-rich foods. Upon completion of the run-in period, participants will follow three 4-week intervention periods with each intervention arm separated by a 4-week washout period. Four weeks after completion of the last intervention arm, participants will be asked to return to the university on two different mornings – separated by two weeks. Measurements of vascular and endothelial function will be taken before and two hours after consumption of either a high or a low-flavanol cocoa beverage. These measurements will serve purely as a positive control for Flow-Mediated Dilation.

Those interested in taking part in the study will first be asked to attend an information session, during which the study will be explained and preliminary blood pressure measurements will be taken. Those deemed eligible based on the blood pressure measurements will be invited to a screening session. During the screening session blood samples will be taken, blood pressure, height, weight and waist circumference will be measured and participants will be asked to complete a short medical history and lifestyle questionnaire. Blood samples taken during the screening will be used to analyse biochemical parameters mentioned in the inclusion criteria (see chapter 4.2). Based on the results of the screening session, those deemed eligible will be asked to take part in the study – which will start with a one-week run-in period. During the one week run-in period, participants will be given dietary guidelines to restrict the consumption of certain flavonoid-rich foods (see Appendix I). This dietary advice will be maintained throughout the study period.

Forty pre-hypertensive subjects will be sequentially randomised to one of the three intervention arms depending on their allocated treatment sequence (see table 5.1). For the three treatments, subjects will be asked to ingest either 160mg of quercetin-3-glucoside (QUER), 100mg of epicatechin (EPI) or placebo capsules (PLA) per day. Supplements will be provided in the form of capsules which will be ingested twice daily – at lunch and in the evening with dinner and with a glass of water.

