Baseline measurements will be taken on the first morning of each intervention arm, following an overnight fast ( $T_0$ ). Hereafter, participants will be asked to consume two capsules per day for four weeks. After the four-week intervention period, follow-up measurements will be taken

at the same time of day as the baseline measurements, again following an overnight fast ( $T_1$ ). This will be done in order to determine the chronic effects of pure flavonoid consumption. Following these follow-up measurements, participants will be asked to consume two final capsules (i.e. the daily dose). Two hours after consumption of these capsules, additional measurements will be taken in order to determine the acute effects of flavonoid supplementation ( $T_A$ ). Changes in values between  $T_0$  and  $T_1$  will allow the analysis of the chronic effects of the intervention as compared to placebo over the 4-week period while  $T_0$  and  $T_A$  will allow analysis of the acute effects during a 2-hour timeframe. For an overview of the timeline of the intervention period and the measurements to be taken, please refer to figure 3.1 and table 3.1.

Participants will be asked to collect 24-hour urine samples during the 24-hour period preceding the baseline and follow-up measurements (6 collections in total). This will be done in order to measure compliance. In addition, 24-hour ambulatory blood pressure measurements will be taken during the 24-hour period preceding baseline and follow-up measurements.

Halfway between each intervention period (i.e. two weeks after the start of each intervention/washout period) participants will be asked to revisit the university ( $T_{1/2}$ ). During these visits, participants will be weighed and a blood sample will be taken. These measurements will be taken at the same time of day as the baseline and follow-up measurements and will last no more than 15 minutes.

Two days prior to the follow-up measurements, participants will be asked to come to the university in order to collect a standardised meal as well as materials for urine collection and 24-hour ambulatory blood pressure monitors. The standardised meal will be consumed the evening prior to the baseline and follow-up measurements.

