#### 4.4 Sample size calculation

With FMD as the primary endpoint, a calculation was carried out to determine optimal sample size for the trial. To date, no studies have been conducted investigating the effects of pure flavonoid supplements in doses proposed for this study. For this reason, the sample size calculation will be based on results from studies conducted using cocoa containing an equivalent amount of epicatechin. Based on these previous studies, a standard deviation of the treatment response of 2.7 is assumed for FMD [23, 25].

Studies investigating the acute effects of cocoa consumption report an increase in FMD of approximately 1.5% – which will be used as the expected effect size for the acute effects of the cocoa intervention. Assuming a power of 0.80 and  $\alpha=0.025$ , and based on a crossover intervention design with multiple testing, 25 subjects would be required to identify a change in FMD of 1.5%. Assuming a dropout rate of approximately 10%, the optimal sample size to investigate the acute effects of flavanol-rich cocoa is 30.

Studies investigating the chronic effects of cocoa consumption report an increase in FMD of approximately 1.3% – which will be used as the expected effect size for the chronic effects of the intervention. Assuming a power of 0.80 and  $\alpha=0.025$ , and based on a crossover intervention design with multiple testing, 35 subjects would be required to identify a change in FMD of 1.3%. Assuming a dropout rate of approximately 10%, the optimal sample size to investigate the chronic effects is 40.

The following formula was used to calculate sample size:

|                                               |                                                                                                                                                       |
|-----------------------------------------------|-------------------------------------------------------------------------------------------------------------------------------------------------------|
| $n = 7.9 \times (SD_{\text{response}} / D)^2$ | $n$ = sample size
$SD_{\text{response}}$ = expected standard deviation of the response to treatment
$D$ = expected effect size due to treatment |
|-----------------------------------------------|-------------------------------------------------------------------------------------------------------------------------------------------------------|

Figure 4.1. Equation used to calculate sample size.

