## 8. STATISTICAL ANALYSIS

Statistical analyses will be conducted based on the intention-to-treat principle. An additional per-protocol analysis will be conducted, however, the intention-to-treat analysis will remain leading. Researchers involved in the statistical analysis will remain blinded to treatment allocation. For statistical significance, a two-tailed p-value of 0.05 will be set.

All data collected during the study will be quantitative. Continuous variables will be expressed as means  $\pm$  standard deviation while categorical variables will be expressed in frequencies. Data will be tested for normality by visual inspection of Q-Q plots and histograms.

Basic descriptive analyses (including age, gender, BMI and blood pressure) will be carried out based on subject characteristics obtained during the screening and baseline measurements.

A repeated measures analysis of variance (ANOVA) will be conducted to compare differences in intraindividual responses to the treatments. Changes from  $T_0$  to  $T_1$  will be used to determine the chronic effect of the intervention. Changes from  $T_1$  to  $T_A$  will be used to determine the acute effects of the intervention. Additional paired t-tests will be carried out to compare baseline values ( $T_0$ ) of outcome measures.

For data that are not normally distributed, a nonparametric Friedman's rank test will be conducted. All statistical analyses will be carried out using the SPSS 19.0 or SAS 9.2 software packages.

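### Section 8 names only global three-arm tests of treatment response, whereas the objective, Section 3 and Section 4.4 call for each flavonoid to be compared with placebo

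*Protocol*

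**What the plan says.** Section 2 sets the primary objective: "To determine the acute and chronic effects of pure epicatechin and quercetin-3-glucoside on vascular and endothelial function", measured by flow-mediated dilation (FMD). Section 3, Part 1, describes a "three-armed, placebo-controlled, double-blind, cross-over trial" and says that the change from T0 to T1 "will allow the analysis of the chronic effects of the intervention as compared to placebo over the 4-week period".

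Section 4.4 uses n = 7.9 × (SD of response / D)², with SD 2.7 and, for the chronic effect, D = 1.3. It cites power 0.80 and alpha 0.025 with multiple testing, and concludes that "35 subjects would be required to identify a change in FMD of 1.3" percent, or 40 after about 10% dropout.

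Section 8 gives the tests of treatment response: "A repeated measures analysis of variance (ANOVA) will be conducted to compare differences in intraindividual responses to the treatments". The fallback is: "For data that are not normally distributed, a nonparametric Friedman's rank test will be conducted". On the level: "For statistical significance, a two-tailed p-value of 0.05 will be set". The one pairwise procedure it mentions is for T0: "Additional paired t-tests will be carried out to compare baseline values". It names no flavonoid-versus-placebo comparison of response.

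**The concern.** With three treatments and no contrast named, the treatment test of a repeated-measures ANOVA is the F test on 2 degrees of freedom, which asks whether any of the three mean responses differ. Friedman's test asks a similar question on ranks. Both also react to a difference between EPI and QUER, which none of the objectives in Section 2 asks about.

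The protocol poses two questions, EPI against PLA and QUER against PLA, and its sample size formula contains one difference. If the analysis stops at the test that Section 8 names, the primary result is one p-value that does not identify the flavonoid. If pairwise comparisons are added later, the choice of pairs, their level and whether they depend on a significant F will all have been made outside the plan.

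**Working it through.** **Inputs.** From Section 4.4: SD 2.7, D = 1.3, power 0.80, alpha 0.025, multiplier 7.9, dropout about 10%. From Section 8: two-tailed 0.05. Completers: 40 × 0.9 = 36.

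**Assumptions added here.** The 2.7 is read as the SD of a within-subject difference between two arms, with equal correlations. The residual variance is then 2.7²/2 = 3.645.

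**The plan's own figure.** 7.9 × (2.7/1.3)² = 34.08, so 35 as stated. 35/0.9 = 38.9, so 39 (stated 40). The formula is the paired calculation for one contrast.

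**Which level the multiplier carries.** (1.960 + 0.842)² = 7.85, which is two-sided 0.05 (or one-sided 0.025). Two-sided 0.025 needs (2.241 + 0.842)² = 9.505. Then 9.505 × (2.7/1.3)² = 41.0, just above 41, so 42 evaluable by the normal formula (44 by the t distribution). 42/0.9 = 46.7, so 47 enrolled. The sample size therefore does not already pay for a two-sided 0.025 level per contrast.

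**Power of the global F at 0.05.** Noncentral F on 2 and 70 degrees of freedom, with λ = 36 × Σ(mean − grand mean)² / 3.645.

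| True effect against placebo | λ | Power of F |
|---|---|---|
| One flavonoid +1.3, the other 0 | 11.13 | 84% |
| Both +1.3 | 11.13 | 84% |
| EPI +1.3, QUER +0.65 | 8.35 | 72% |
| EPI +0.65, QUER −0.65 | 8.35 | 72% |

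The power of F depends on the other flavonoid's effect, which the Section 4.4 formula does not contain.

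**Power of one placebo contrast.** Pooled error, 70 degrees of freedom, noncentrality 1.3/(2.7/√36) = 2.89: 81% at two-sided 0.05 and 72% at two-sided 0.025.

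**F at 0.05, then pairwise at 0.05 (simulation).** EPI minus PLA is detected in about 77% of trials when the QUER effect is 0 or +1.3, and in about 71% when it is +0.65.

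**How often the global test and the contrasts disagree (simulation).** The table gives the share of significant F tests in which neither placebo contrast reaches two-sided 0.05.

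| True effect against placebo | Share |
|---|---|
| Both +1.3 | about 0.01% |
| EPI +1.3, QUER 0 | about 7% |
| EPI +0.65, QUER −0.65 | about 26% |

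In the other direction, with EPI +1.3 and QUER +0.65, F is non-significant while EPI minus PLA is significant in about 11% of trials if the contrast is tested at 0.05, and in about 3.5% if it is tested at 0.025.

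**The case against.** The strongest reply is that Section 8 names a model and not a single test. It does not say that inference ends with the overall F, nor does it exclude contrasts. Section 3 gives placebo as the comparator, Section 4.4 mentions multiple testing, and contrasts following an ANOVA are often left to a statistical analysis plan, which is not at hand. This stands in part: a reader might infer that the protocol rules out flavonoid-versus-placebo tests, and it does not. What remains is that the protocol is not merely silent. It fixes a global test at 0.05, spells out pairwise tests for T0 only, and sizes a single difference with a different alpha. Those sections do not describe the same analysis.

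Three stronger readings are tempting and are not supported.

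- **That the F test is often significant for the wrong reason.** The 26% figure needs QUER to be worse than placebo by half the planned effect. Nothing in the protocol suggests that. At the planned +1.3 the share is between about 0% and 7%. Moreover, if EPI and QUER truly differ, at least one of them differs from placebo; the disagreement is only about which tests reach significance.
- **That the global test loses power.** The comparison of 81% with 72% sets a contrast at 0.05 against F at 0.05 with no allowance for two contrasts. At 0.025 the contrast has 72%, the same as F in that scenario. With one or both flavonoids at +1.3, F has 84%.
- **That F must not serve as a gate.** With three arms, F at 0.05 followed by pairwise tests at 0.05 controls familywise error under the ANOVA model. In most of the cases above it detects EPI minus PLA at least as often as ungated contrasts at 0.025.

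The introduction also calls it important to learn which flavonoids are most responsible for the effect. EPI against QUER is therefore a reasonable secondary comparison, though not a stated objective.

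**Conclusion.** The point holds as a mismatch within the protocol. Section 8 tests treatment response only globally, at 0.05, while the objective and Section 3 ask for each flavonoid against placebo and Section 4.4 sizes one paired difference with alpha 0.025. This follows from the text and needs no power assumption.

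Its practical size is moderate. At the planned effect, a significant F is nearly always accompanied by a significant placebo contrast at 0.05. What is lost is a pre-specified statement of which flavonoid, by how much, and at what error rate. The power figures rest on 36 completers, 2.7 as the SD of a between-arm difference, and equal correlations. On those assumptions the 80% in Section 4.4 describes neither the global F (72% to 84% in the cases shown) nor two error-controlled contrasts (about 71% to 77%).

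**What to change.** In Section 8, pre-specify EPI minus PLA and QUER minus PLA, from the same repeated-measures model, as the primary comparisons, each with an estimate and a confidence interval. State one procedure that controls familywise error: either two-sided 0.025 per contrast, or the overall F at 0.05 followed by pairwise tests at 0.05. Make EPI against QUER secondary. If the Friedman fallback is kept, tie it to the same two comparisons.

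The change needs wording but no new measurements. Its cost is that the power claim in Section 4.4 must be restated. On the assumptions above, power per contrast is about 72% at two-sided 0.025. By the F-gated route it is about 77% when the other flavonoid's effect is 0 or +1.3, and about 71% when it is +0.65. Keeping 80% at two-sided 0.025 would take 42 to 44 evaluable subjects, or about 47 enrolled on the lower figure.

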## SUMMARY

**Rationale:** Epidemiological evidence supports the hypothesis of a protective effect of flavonoids on cardiovascular disease (CVD). To date, most intervention studies have investigated the effects of flavonoid containing-foods (such as tea and cocoa) on cardiovascular health while studies using pure flavonoids have frequently used high doses. As such, few studies have been conducted investigating the effects of dietary doses of pure flavonoids on markers of cardiovascular health in a large population over a prolonged period of time.

**Objective:** To determine the acute and chronic effects of pure flavonoid supplementation on markers of vascular function in (pre)hypertensive subjects.

**Study design:** The study will be conducted as a three-armed, randomized, placebo-controlled, double-blind, cross-over trial.

**Study population:** 40 apparently healthy men and women between the ages of 30 and 80, with untreated (pre)hypertension will be enrolled on the study. (Pre)hypertension will be defined as a systolic blood pressure between 125 and 160 mmHg.

**Intervention:** The study will be separated into two parts. Part 1 will investigate the effects of pure flavonoid supplements while Part 2 will investigate the effects of a flavanol-rich coca drink.

For Part 1 of the study, participants will first complete a 1-week run-in period during which they will be advised to avoid consumption of foods high in flavonoids. Upon completion of the run-in period, participants will be sequentially randomized to the following three intervention arms for four weeks;

- 1) 160mg per day quercetin-3-glucoside in capsule form;
- 2) 100mg per day epicatechin in capsule form;
- 3) Placebo in capsule form

A washout period of 4 weeks will be included between the interventions, during which participants will be advised to maintain the dietary advice of restricted flavonoid consumption. Measurements of vascular and endothelial function will be taken before and after each intervention arm. In addition, measurements will be taken before, and 2 hours after consumption of the supplements, on the final study day of each intervention.

Four weeks after completion of the last intervention arm, participants will be asked to take part in Part 2 of the study. Part 2 will be optional and participation will not be obligatory for

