the participants. Those who opt to take part in Part 2 will be asked to return to the university on two different mornings – separated by two weeks. Measurements of vascular and endothelial function will be taken before and two hours after consumption of either a high or a low-flavanol cocoa beverage. These measurements will be used to compare the effects of pure epicatechin and epicatechin in cocoa on FMD and will also serve as positive control for FMD.

**Main study parameters/endpoints:** The primary study parameter is the percentage change in Flow-Mediated Dilation (FMD) before and after the intervention period. Additional study parameters include (biochemical) markers of vascular and endothelial function as well as systolic and diastolic blood pressure.

**Nature and extent of the burden and risks associated with participation, benefit and group relatedness:** The risks of participating in the study are negligible, while the burden is low. For all supplements used, a safety report is provided (see Appendix II). The dosage used for the supplements is consistent with 3 times the P90 of the habitual intake of the Dutch population. As such, the dosage used is in line with what can be achieved through a high-flavonoid diet.

All participants will be asked to visit the university for an initial information session as well as a screening session. During the study, participants will attend six measurement days – separated by 4 weeks. Blood pressure and FMD measurements will be taken at all visits. Blood samples will be taken at all visits, except during the information session – this can be considered the greatest burden for participants. FMD can be considered a small burden due to minor discomfort during the measurement as a result of venous occlusion for 5 minutes and the necessity to remain still during the reading. Six 24-hour urine samples will be collected and 24-hour ambulatory blood pressure will be measured which could be considered an inconvenience to participants.

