## 6. METHODS

### 6.1 Study parameters/endpoints

#### 6.1.1 *Main study parameter/endpoint*

The main study parameter is the percentage change in FMD before and after the intervention period.

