### 6.3 Randomisation and Blinding

*Randomisation:*

Subjects will be sequentially randomly allocated to the various intervention arms based on their allocated treatment sequence (see table 5.1). Due to the fact that there are three intervention arms, six possible treatment sequences exist . Allocation to treatment sequence will be performed by an independent investigator employed at Wageningen University, who is not involved in the study. To maintain confidentiality, this investigator will be provided with an identification number for each participant and will not come into contact with the participants. At the start of each intervention period, another researcher will provide the participants with the materials needed for their allocated intervention. This researcher will not be involved in the collection of anthropometrical, physiological or biochemical data.

Table 5.1. Possible treatment sequences for the FLAVO-study.

| Treatment sequence |             |             |             |
|--------------------|-------------|-------------|-------------|
| 1                  | Placebo     | Epicatechin | Quercetin   |
| 2                  | Placebo     | Quercetin   | Epicatechin |
| 3                  | Epicatechin | Placebo     | Quercetin   |
| 4                  | Epicatechin | Quercetin   | Placebo     |
| 5                  | Quercetin   | Epicatechin | Placebo     |
| 6                  | Quercetin   | Placebo     | Epicatechin |

*Blinding:*

Researchers and medical staff will remain blinded towards the intervention. The company providing the capsules for the intervention (Het Gelre Apotheek, Apeldoorn) will be asked to deliver the capsules with a specific code for each treatment. The company will be asked to keep a record of the coding and will provide this code upon completion of the study. In case of serious adverse events, a subject's GP may request unblinding of the treatment.

Upon completion of the study, subjects will be asked to report the sequence of intervention groups they thought they had been allocated to. In addition, all subjects will be informed of the correct sequence of interventions they were allocated to – this will be conducted by the same researcher who provided the subjects with their materials during the intervention.

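### The chronic FMD effect is analysed as a raw T0-to-T1 change; adjusting T1 for the period's own T0 would be more precise, by an amount that depends on a correlation the protocol does not give

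*Protocol*

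**What the plan says.** Protocol section 6.1.1 sets the primary endpoint: "The main study parameter is the percentage change in FMD before and after the intervention period". Section 8 names a repeated measures ANOVA that "will be conducted to compare differences in intraindividual responses to the treatments", and says that changes from T0 to T1 "will be used to determine the chronic effect of the intervention". The period baseline has one other use there: "Additional paired t-tests will be carried out to compare baseline values". No baseline covariate is named.

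The data for an adjustment are already planned. Section 3 states: "Baseline measurements will be taken on the first morning of each intervention arm, following an overnight fast". Table 3.1 lists FMD at both T0 and T1. On timing, the Summary says that "participants will attend six measurement days – separated by 4 weeks" and that "A washout period of 4 weeks will be included between the interventions". Section 6.3 adds that "six possible treatment sequences exist" for the three treatments.

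**The concern.** A baseline is subtracted to remove stable differences between people. In a crossover those differences already drop out, because each subject receives all three treatments. What remains in T0 is mostly its own visit-to-visit error. Full subtraction carries that error into the treatment contrast unless T0 and T1 errors within a subject are very strongly correlated.

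The visit schedule gives little reason to expect that. The six main visits are equally spaced at four weeks, so the T1 of one period is as close in time to the next period's T0 as to its own.

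At stake is precision on the primary endpoint of a 40-subject trial. It could be recovered from measurements already planned.

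**Working it through.** **Inputs.** From section 4.4: SD 2.7, chronic effect 1.3 FMD points, power 0.80, dropout about 10%, 40 enrolled (40 × 0.9 = 36 completers). From section 8: two-tailed 0.05. From the Summary: six main visits four weeks apart. Assumed, because the protocol does not give it: r.

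**The plan's own figure.** n = 7.9 × (2.7/1.3)² = 34.08, rounded up to 35, as stated. The multiplier 7.9 is close to (1.960 + 0.842)² = 7.85, which corresponds to two-sided 0.05. Section 4.4 cites 0.025, so power is shown below at both levels.

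**Variance of the contrast.** Let σ² be the within-subject error variance at one visit. Let r be the correlation of the T0 and T1 errors of the same period, with errors in different periods uncorrelated. For two treatments compared within one subject:
- change score: 2 × 2σ²(1−r) = 4σ²(1−r)
- T1 adjusted for T0: 2σ²(1−r²)
- ratio, adjusted to change: (1+r)/2

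The ratio is below 1 for every r below 1, so the direction does not depend on the assumption. More generally, the same ratio holds with r read as the correlation between the T0 difference and the T1 difference of the two treatments.

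**What the spacing implies for r.** If a plain subject effect explains all correlation between visits, r = 0. If an AR(1) process with lag-one correlation φ is added, then for adjacent periods r = (φ−φ³)/[2(1−φ²)] = φ/2, which is at most 0.5. For periods 1 and 3 it is at most 0.75.

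Simulation of the full design (36 subjects, six sequences, fixed subject and period effects, estimated baseline slope) gave these variance reductions:
- independent errors: 48%
- φ=0.3: 40%
- φ=0.5: 33%
- φ=0.7: 26%
- φ=0.9: 21%
- half of the within-subject variance is measurement noise, φ=0.7 or 0.9: about 41%
- extreme case, φ=0.95 with no noise and no separate subject effect: 18%

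**Power.** This step assumes that 2.7 is the SD of the between-treatment difference in changes. The adjusted SD is 2.7 × √[(1+r)/2], and the noncentrality is 1.3 × √36 / SD. Power is from the noncentral t for a paired comparison, with one degree of freedom removed for the covariate.

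| Analysis | Variance reduction | SD | Noncentrality | Power, two-sided 0.05 | Power, two-sided 0.025 |
|---|---|---|---|---|---|
| Change score | – | 2.70 | 2.89 | 80% | 71% |
| Adjusted, r=0.8 | 10% | 2.56 | 3.05 | 84% | 76% |
| Adjusted, r=0.7 | 15% | 2.49 | 3.13 | 86% | 78% |
| Adjusted, r=0.5 | 25% | 2.34 | 3.34 | 90% | 83% |
| Adjusted, r=0.3 | 35% | 2.18 | 3.58 | 94% | 89% |
| Adjusted, r=0 | 50% | 1.91 | 4.09 | 98% | 95% |

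**The case against.** The strongest defence is that a period-specific change in a randomised crossover is valid, unbiased and common, and that section 8 does not forbid a covariate in a later analysis plan. Validity stands, so this is a matter of efficiency and not an error. But the protocol states the analysis variable and does not leave it open, so the choice can fairly be questioned here.

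Several stronger readings are tempting, and the protocol does not support them.

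- **That 25% to 50% of the variance is lost as a fact.** That range is simply r from 0.5 to 0, and no within-subject correlation is given. At r of 0.7 to 0.8 the saving is 15% to 10%.
- **That adjustment would more than make up a power shortfall.** On these assumptions a shortfall exists only at two-sided 0.025. Section 8 tests at 0.05, where the change score already has 80%. Even at 0.025, reaching 80% needs r of about 0.6 or less and 2.7 as the SD of the difference. Section 4.4 ties 2.7 only to the treatment response. If it is the SD of a one-period change and changes are uncorrelated between periods, the difference has SD 2.7 × √2 = 3.82. Power at 0.025 is then 39%, rising to 51% (r=0.5), 58% (r=0.3) or 71% (r=0).
- **That the endpoint is a relative change in FMD, at odds with section 4.4.** Section 6.4.1 defines the percentage as the dilation itself, maximum minus baseline diameter over baseline diameter. This largely answers the point.
- **That the same gain applies to the acute effect.** T1 and TA are two hours apart on one morning, so the four-week-spacing argument does not carry over, and no figure has been worked out.
- **That the paired t-tests of T0 are wrong and must go.** The protocol gives no purpose for them. They could serve as a descriptive check for carry-over. They cannot correct a chance baseline difference.

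**Conclusion.** The point holds as an efficiency point on the chronic FMD contrast. The planned change score is less precise than T1 adjusted for the same-period T0 for any r below 1. How much less rests on an r that the protocol does not report. The equal visit spacing favours low to moderate values, where the variance falls by about 25% to 50%, but smaller savings cannot be excluded. The power figures rest further on reading 2.7 as the SD of the between-treatment difference in changes; the variance ratio does not. No bias is alleged. The improvement is worth making, but the trial's validity does not depend on it.

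**What to change.** In section 8, state the chronic analysis as a model for %FMD at T1, in percentage points as defined in section 6.4.1, with treatment, period and subject effects and the same-period T0 as covariate. Use fixed subject effects, or split the baseline into the subject's mean and the deviation of each period from it, so that between-subject differences in baseline do not distort the within-subject adjustment. The treatment contrast estimated is the same as with change scores.

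The paired t-tests of T0 may stay as description, but should not be relied on to deal with chance baseline differences.

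The cost is one degree of freedom and a changed model sentence, settled before unblinding. No extra measurement is needed.
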